**Abstract**

**Background:** Remote access to health care optimizes the use of local resources, facilitates access to care and minimizes the risk of covid-19 contagion. This study aims to describe indicators of feasibility including patient recruitment, attendance, discomfort, satisfaction and travel time and cost savings of virtual telemedicine consultations for patients with dementia. **Methods:** Virtual telemedicine consultation with patients and their caregivers will be similar to a routine face-to-face consultation. We will perform a single-center one-arm study with indicators of feasibility as the study primary endpoints.

**Ethics and dissemination:** The study is approved by the Research Ethics Committee of Hospital Universitário Walter Cantidio and all participants will provide their written informed consent (register number 31779920.1.0000.5045).

Trial results will be disseminated via peer reviewed journal articles and conference presentations, reports for organisations involved with PD and for participants. Trial registration number Registro Brasileiro de Ensaios Clínicos Registry (RBR-9xs978).

**Keywords**

telemedicine, dementia, feasibility studies

**Bullet points:**

- This is a feasibility study of a telemedicine approach for patients with dementia attending a public health care center in Northeast Brazil.
- The telemedicine intervention may be a good strategy for avoiding a stressful situation of long waits in medical rooms for face-to-face consultations and the risk of coronavirus contagion in the current COVID-19 pandemic.
- Telemedicine consultations for delivering care for patients with dementia may be feasible and effective in Brazil’s public health system.

**Telemedicine for delivering care for patients with dementia at a tertiary hospital in Northeast Brazil: impact of telegeriatrics during the COVID-19 pandemic (TeleGeriatrics Protocol)**

**Background and rationale**

On March 18, 2020 government’s authorities imposed social distancing measures and public gathering restrictions in the state of Ceará, Northeast Brazil, in response to the COVID-19 pandemic.^1^ Elective face-to-face consultations had to be rescheduled and the need for health care during the pandemic called for telehealth solutions. National initiatives have been recently launched to review and update previous restrictions to telehealth practice and expand its use as a solution for improving care provided in the national state-funded health system.^2^ Brazil’s Ministry of Health issued a new ordinance authorizing the practice of telemedicine in public and private settings and operationalizing measures to handle the pandemic.

Brazil’s aging population has grown at a fast rate in recent decades.^3^ There has been also an increase in the prevalence of neurodegenerative and neuropsychiatric diseases, especially dementias. Social and economic consequences of dementias are profound in the Brazilian population.^4^ Neuropsychiatric symptoms of dementia are common and they are often distressing for patients and caregivers. Neuropsychiatric presentations appear in various types of dementia and at different stages, and symptom frequencies and presentation may vary.^5^ Given the enormous burden of dementia for patients and caregivers, in addition to the fact that older age is associated with more multimorbidity and clinical complications requiring monitoring and control, ongoing individualized approaches are imperative for the management of this vulnerable population group.^6^

Many patients with neurodegenerative disease, particularly those living in rural areas, can likely benefit from improved health care access via telemedicine in both the short- and the long-term.^7^ Distance, functional disability, uneven geographic distribution of health care professionals, lack of social support, work constraints, travel cost and associated risks can be barriers to access of older people to specialized care.^8,9^ Remote access to health care optimizes the use of local resources, facilitates access to care and minimizes the risk of covid-19 contagion.^10^ To the best of our knowledge, no study has assessed the feasibility of using telemedicine for delivering care to patients with dementia in Brazil’s public health system. This study aims to describe indicators of feasibility including patient recruitment, attendance, sense of safety and satisfaction and travel time and cost savings. The purpose is to examine the feasibility of geriatric consultations via telemedicine for delivering care to patients with dementia in the public health system.

Hypothesis

We hypotesize that TeleGeriatrics will have good indicators of feasibility of geriatric consultations via telemedicine for delivering care to patients with dementia in the public health system.

SPECIFIC OBJECTIVES

Primary objective

To determine the feasibility of a telehealth video consultation using WhatsApp© for delivering care directly at home to patients with dementia in Brazil’s public health system.

Secondary objectives

To ascertain the perceived impact of covid pandemia worsening their medical conditions

**Methods/Trial design**

*Study design*

We will perform a single-center one-arm study to describe indicators of feasibility (including patient recruitment, attendance, acceptance, sense of safety satisfaction and travel time and cost savings) of virtual medical consultations. Elegible patients will be recruited from outpatient clinic’s medical appointment scheduling list.

The flow diagram of the protocol is detailed in figure 1. The study protocol was described according to the Standard Protocol Items: Recommendations

for Interventions Trials statement (SPIRIT)^11^.

Study Setting

The study will be conducted at the Geriatrics Department of Hospital Universitário Walter Cantídio (HUWC) in Fortaleza, Brazil, between May 1^st^ and December 31, 2020. It was approved by HUWC Ethics Committee (registration number 31779920.1.0000.5045) and the Brazilian Trial Registry (REBEC) RBR-9xs978. All patients or their caregivers will sign a written informed consent form.

The Hospital Universitário Walter Cantídio (HUWC) of Universidade Federal do Ceará (UFC) is a reference centre for training human resources and developing

health research. Being integrated with the Public Health System, it also acts as an important centre for healthcare in Ceará. As a reference centre for teaching, it serves as an internship field for undergraduate and graduate students of UFC’s Medicine, Nursing, Physiotherapy and Pharmacology courses.

*Study participants*

Participants will be consecutively recruited from the dementia outpatient clinic’s medical appointment scheduling platform at HUWC. Those who will meet the inclusion criteria will be selected until the required recruitment period (a total of eight months) is achieved. The patients were will be invited in a phone call to participate in the feasibility study. Those who agree to participate will be screened for eligibility and, if eligible, they will be asked to attend a remote medical consultation. The WhatsApp-based intervention includes video and text messages. Recent studies have emphasized broad opportunities of WhatsApp messenger as an adjunctive tool for telemedicine.^12^ We chose this tool because our sample is familiar with the use of this technology in their everyday life.

Eligibility criteria

The eligibility criteria include previous diagnosis of dementia syndrome according to the diagnostic criteria of the Diagnostic and Statistical Manual of Mental Disorders 5th edition (DSM-5) and receiving care at the hospital’s dementia outpatient clinic in face-to-face consultations in the preceding 12 months. Patients will be excluded if they do not feel comfortable with virtual consultations, do not have the required communication technology available or their caregiver is not available to attend the remote consultation.

*Study intervention*

The team will review medical charts before and during the consultation to check for comorbidities and medication use. The remote consultations will follow the order of patients in the waiting list; they will be conducted once a week during morning hours following an interview procedure similar to face-to-face consultations. Since the study setting is a public teaching hospital, consultations will be carried out by medical residents and interns during their rotation in this service under the supervision of one geriatrician who is a hospital employee.

The remote consultations will involve treatment approaches, health promotion recommendations, drug prescription, complementary diagnostic tests and referral to other health providers. Patients will be sent education materials with health recommendations and medication use schedules to improve their adherence (supplementary files 1 and 2). We developed two different education materials (PDF files). Patients with preserved mobility received education materials including recommendations on healthy eating, sleep hygiene, physical activity, fall prevention and non-pharmacological approaches for urinary incontinence. Those with limited mobility received materials with recommendations for healthy nutrition, sleep hygiene, approaches to reduce the risk of aspiration pneumonia and prevent skin lesions, contractures and pain.

The intervention is designed as a one-time consultation (see flowchart in Figure 1) before the next face-to-face consultation. Remote reassessment will be determined by the attending geriatrician or at caregivers’ request. An urgent face-to-face appointment will be provided when a physical examination is required.

We will use the Research Electronic Data Capture (REDCap)^13^ software for data collection and management.

Criteria for discontinuation

If there is suspicious that the patient doesn’t have dementia diagnosis or if the patient does not have a face-to-face consultation in the prior 12 months, the virtual appointment will be concluded but the patient will not be included in the analysis and the outcomes measures will not be collected.

*Sample size*

The study sample was drawn consecutively among those meeting the eligibility criteria during the recruitment period from May to December 2020. The period of recruitment was established based on logistics and financial considerations.

*Characterization measures*

Data will be collected through medical chart review and patient questionnaires. Baseline and demographic data include age; gender; type of caregiver (formal [paid]/informal [unpaid]); dementia duration; presence of chronic comorbidities; medication use; rehabilitation care; fall events; neuropsychiatric symptoms; sleep disturbance complaints; constipation; dysphagia; and urinary incontinence. The participants will also be asked about functional decline due to social restrictions during the pandemic.

We will administer three dementia-related geriatric questionnaires: The Functional Assessment Staging Tool (FAST); the Katz Activities of Daily Living (ADL) scale; and the Abbreviated Mental Test 4 (AMT4). The FAST is easy to administer and has excellent validity for assessing functional capacity over the course of Alzheimer’s disease and it is also used in other dementias^14^. It assesses a continuum over 16 successive stages, from normality through more severe dementia stages.^15^ The FAST scale has 7 stages: 1, normal cognition; 2, subjective cognitive impairment; 3, mild cognitive impairment; 4, mild dementia; 5, moderate dementia; 6, moderately severe dementia; and 7, severe dementia. Stages 6 and 7 are further subdivided into substages: substages 6a to 6e, moderately severe dementia; substages 7a to 7c, severe dementia; and substages 7d to 7g, very severe dementia.^16^ All patients in our study were FAST stages 4 to 7.

We will use the AMT-4 to assess cognitive function. Brief cognitive tests such as the AMT-4 and AMT-10 have been widely used in acute care units of UK hospitals and shown good sensitivity for detecting delirium as well as previously diagnosed dementia.^17^ The AMT-10 was not superior to the AMT-4 in a validation study conducted in Brazil.^18^ The cut-off points of three or more correct answers (AMT-4) showed an even higher sensitivity (80%) than the ten-item test, with good specificity (88%) and good reliability^19^. The four questions that will be asked are: 1 – current time (correct answer: ±1 hour); 2 – home address instead of hospital name as the patients were at home; 3 – date of birth; 4 – counting backwards by 1 from 20 to 1.

The Katz scale is widely used to assess activities of daily living (ADLs) rated on a scale of 0 to 6. It has been developed as a predictor of treatment outcomes in older people and patients with chronic conditions. This 6-item scale grades performance on self-care activities following a hierarchy of complexity: feeding; continence; transferring; personal hygiene; dressing; and bathing. Independence means being able to perform these activities without supervision, guidance or active personal assistance. The assessment is based on actual performance, not skills. Those refusing to perform an activity are considered dependent, even though they are believed to be capable of doing it. We administered a version of the Katz scale that was translated and culturally adapted to Brazilian Portuguese by Lino et al. (2008), where higher scores indicate more dependence.^20^

Primary outcome measures

*Recruitment rate*

Eligible patients will be asked to sign an informed consent form and an appointment will be scheduled using WhatsApp messenger or via telephone. They will receive some instructions to optimize the remote consultation: choose an adequate room with strong wi-fi signal; have their caregiver or a family member present during the entire appointment; and have their most recent test results and list of medications at hand.

The recruitment rate for telemedicine consultations will be calculated by the number of patients agreeing to participate in the study divided by total number of patients which we will have attempted to contact.

*Attendance*

The attendance rate will be calculated by the proportion of virtual medical consultations completed as scheduled. The intervention will be considered feasible if at least 80% of the consultations could be completed.^21^

*Acceptance*

A self-administered questionnaire will be used to evaluate whether our telemedicine intervention is feasible, safe, satisfying and well-accepted for future use. This questionnaire will be answered with the help of the caregiver for patients with early dementia and by the caregivers themselves for patients with moderate to severe dementia. They will be asked to inform the questionnaire’s respondent. The questionnaire consists of 12 questions with a visual analogue scale (VAS) to evaluate satisfaction (worst on the left end and best on the right end) and one additional open-ended question. The participants will be asked to mark the point (face) on a horizontal line that is representative of their level of satisfaction. For each question, they can select only one option.

The questionnaire has five domains: feasibility (items 1–2); sense of safety (items 3–5); appreciation and satisfaction (items 6–7); effectiveness (items 8–9); acceptance and future use of the intervention (items 10–12). Lower scores indicate lower perceived interest, safety, satisfaction, acceptance and benefits of telemedicine. We also include an open-ended question for suggestions and comments. The VAS scale will be sent on WhatsApp as a Google Drive link. This same questionnaire has been administered by other authors^22,23^. If the participants do not complete the questionnaire within 45 days, it will be administered through a phone interview with the participants’ caregivers.

*Discomfort*

Patient discomfort during consultation will be assessed by the number of consultations with internet connection issues and/or the interviewer’s perception of patient behavior changes divided by the number of consultations.

*Travel time and cost savings*

Information on travel time and costs will be collected during the interview to capture both time and financial burden of face-to-face consultations. They will be asked about transportation, average travel time from the clinic to their home, and travel expenses.

*Statistical analysis*

For numerical variables, data will be presented as means, standard deviations and medians. For categorical variables, data will be described as frequencies.

Data Collection Methods

The team will be trained and will meet before the trial onset to consolidate data collection procedures.

Data Mangement

The study data will be collected and managed using the REDCap electronic data collection and management tool hosted at the Clinical Research Unit of the UFC.

The original study forms will be entered in REDCap.

ETHICS AND DISSEMINATION

We are committed to disseminating the methods and conclusions of the TeleGeriatrics Study to the interested research groups. Therefore, our disclosure plan after completion of the study covers the following: scientific meeting with residents, students, assistant doctors and researchers of HUWC in which the present study design, results and interpretation will be presented.

CONSENT OR ASSENT

The recruiting medical team will present the study details to the patients and will apply the consent form. The recruitment team will encourage patients put forth their doubts and assure them that their privacy will be preserved, and they are free to withdraw from the study anytime.

CONFIDENTIALITY

All information of the study patients will be stored in a locker in an area with limited access. The database will be registered and stored in REDCap, with password protected access systems.

DECLARATION OF INTERESTS

The author(s) received no specific funding for this work. There is no conflict of interests.

ACCESS TO DATA

The project data sets will be hosted on the REDCap, to which the project’s principal investigators will have direct access through a valid password.

ANCILLARY AND POST-TRIAL CARE

The study patients will continue to be assisted at the movement disorders outpatient clinic of HUWC by a team of neurologists and geriatricians.

DISSEMINATION POLICY: TRIAL RESULTS

Our purpose is to dedicate our efforts to reduce the interval between the completion of data collection and the dissemination of study results to an absolute minimum. We expect to take about 6 months to prepare the document of final results for an appropriate journal. The results of the study will be released to participating physicians, referring doctors, patients and the medical community.

|  |
| --- |

Figure 1. CONSORT 2010 Flowchart

Eligible

Assessment for eligibility

Excluded

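### Dropping patients whose dementia diagnosis is doubted around the consultation removes mainly completed consultations from the attendance rate and biases it downward against the 80% rule

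*Protocol*

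**What the plan says.** Under Criteria for discontinuation the protocol names two triggers: a suspicion that the patient does not have dementia, "or if the patient does not have a face-to-face consultation in the prior 12 months". In either case "the virtual appointment will be concluded but the patient will not be included in the analysis and the outcomes measures will not be collected".

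Under Study participants, eligibility is settled before anyone is scheduled: "Those who agree to participate will be screened for eligibility and, if eligible, they will be asked to attend a remote medical consultation". The Eligibility criteria already require a previous DSM-5 diagnosis of dementia and in-person care at the clinic within the preceding 12 months. Under Study intervention, "The team will review medical charts before and during the consultation", although the stated purpose of that review is comorbidities and medication, not eligibility.

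Attendance is one of the primary outcome measures: "The attendance rate will be calculated by the proportion of virtual medical consultations completed as scheduled". It carries the protocol's only numerical success rule: "The intervention will be considered feasible if at least 80% of the consultations could be completed".

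**The concern.** Patients have been screened before they are invited to a consultation, so the discontinuation rule acts on people already judged eligible and scheduled. It is written around an appointment that takes place. A clinical suspicion that someone does not have dementia is formed mainly by talking to that person and the caregiver. A patient who does not attend gives much less occasion for it, and the protocol describes no matching check on non-attenders.

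The exclusion is therefore linked to the outcome being measured. A completed consultation can be taken out of both numerator and denominator, while a no-show who would have raised the same doubt remains in the denominator. The attendance rate is pulled below its true value, and a service that meets the 80% rule could be reported as missing it.

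The rule also stops outcome collection. Discomfort and acceptance would be lost for consultations that were actually delivered, and no later analysis plan can restore data that were never collected.

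**Working it through.** **Inputs from the protocol.** The threshold is 80% of consultations completed (Attendance). Patients caught by the rule are left out of the analysis (Criteria for discontinuation). The protocol gives no sample size, expected attendance or expected number of exclusions, so there is no figure of its own to reproduce.

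**Assumed inputs.** True attendance A is taken as 80% to 90%, and the share m of attenders dropped as 2% to 20%. Neither range comes from the documents.

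**Formula.** If a share m of attenders leaves numerator and denominator and all no-shows stay, then

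reported rate = A(1 − m) / [A(1 − m) + (1 − A)].

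This is below A whenever m > 0 and A < 1.

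**Worked case, A = 82%.**
- m = 5%: 0.82 × 0.95 = 0.779, and 0.779 / (0.779 + 0.18) = 81.2%.
- m = 10%: 0.82 × 0.90 = 0.738, and 0.738 / (0.738 + 0.18) = 80.4%.

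**Over the assumed range.**

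| True attendance | m = 2% | m = 5% | m = 10% | m = 20% |
|---|---|---|---|---|
| 80% | 79.7% | 79.2% | 78.3% | 76.2% |
| 82% | 81.7% | 81.2% | 80.4% | 78.5% |
| 85% | 84.7% | 84.3% | 83.6% | 81.9% |
| 90% | 89.8% | 89.5% | 89.0% | 87.8% |

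The 80% row starts exactly on the threshold, where any deletion reverses the conclusion, so it should not be read as typical.

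**Share of attenders that must be dropped to bring the rate down to 80%.** Setting the reported rate to 0.80 gives m = 1 − 0.80(1 − A) / (0.20 A):
- A = 81%: 1 − 0.152/0.162 = 6.2%
- A = 82%: 1 − 0.144/0.164 = 12.2%
- A = 85%: 1 − 0.120/0.170 = 29.4%
- A = 90%: 1 − 0.080/0.180 = 55.6%

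**In counts (illustrative).** Of 100 scheduled consultations 82 are completed, which is 82.0%. Dropping 10 completers gives 72/90 = 80.0%; dropping 11 gives 71/89 = 79.8%.

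**If no-shows are also excluded.** If the same 10% of no-shows were removed, the rate would be 0.738 / (0.738 + 0.162) = 82.0%, with no bias. If 10% of attenders but only 5% of no-shows were removed, it would be 0.738 / (0.738 + 0.171) = 81.2%. The bias therefore needs only that exclusion be more frequent among attenders, not that it be confined to them.

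**The case against.** Several points can be made for the plan.

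- **Only attenders can be excluded.** A reader might infer this, but the text does not say it. Charts are looked at beforehand, so doubt could arise about someone who then fails to attend, and the 12-month trigger can be checked in records for everyone. This stands. The point applies to the suspicion trigger and to mainly, not exclusively, attenders.
- **The attendance count may be untouched.** Attendance is defined per consultation, while the exclusion is of the patient, and the protocol never states that such consultations leave the attendance rate. That is fair as to wording. But the intervention is planned as a single consultation per patient, attendance is a primary outcome, and it is not exempted from the exclusion. Leaving the consultation out is the natural reading.
- **The bias is small and conservative.** It runs downward, and entry already requires a dementia diagnosis, so exclusions may be few. This stands and limits the weight of the point.
- **Inconvenient consultations could be removed.** A reader might infer that the rule lets unsatisfactory consultations drop out of discomfort and acceptance, or that the interviewer who rates discomfort also decides the exclusion. The documents support neither. The triggers are diagnosis and visit date, the protocol does not say who forms the suspicion, and a geriatrician supervises the consultations.
- **The target population is people with dementia.** Leaving out those thought not to have it is a defensible choice stated in advance. It answers a somewhat different question, and a sensitivity analysis can show that result without making it the main one.

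**Conclusion.** The concern holds in a limited form. As written, the rule takes mainly completed consultations out of the attendance rate and biases it downward against the 80% threshold. It cannot create a false finding of feasibility. A false finding of non-feasibility is possible only if true attendance is a little above 80% or exclusions are numerous: about 12% of attenders at a true 82%, and more than a quarter at 85%. The documents give no exclusion rate, so the actual size is unknown and a large distortion should not be claimed.

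The conclusion rests on two readings: that exclusion from the analysis includes the attendance rate, and that diagnostic doubt arises more often in patients who are seen than in those who are not. The loss of discomfort and acceptance data from delivered consultations follows directly from the text; the direction of any effect on those outcomes is unknown. The rule is worth changing because it affects a primary outcome and the change costs little.

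**What to change.** 1. Confirm the previous DSM-5 diagnosis and the in-person visit within 12 months from records at the eligibility screening that already precedes scheduling. This settles the 12-month trigger. It does not prevent later clinical doubt, which the next steps cover.
2. Count every scheduled consultation in the attendance rate, with completed ones counted as completed whatever diagnostic doubt arises afterwards.
3. Collect discomfort and acceptance for every consultation delivered. No-shows have no consultation to rate and do not enter these two outcomes.
4. Leave the recruitment rate as defined: patients agreeing over patients with attempted contact.
5. Record later diagnostic doubt as a variable, report how many patients it concerns, and show a sensitivity analysis without them.

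The cost is a change of wording, a records check placed within an existing step, and a few more questionnaires. The downside is that a few patients with a doubtful diagnosis stay in the main analysis. The care that patients receive does not change.

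### The 80% attendance threshold is written as sufficient for calling the whole intervention feasible, although attendance is measured only after patients who decline or are excluded have left

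*Protocol*

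**What the plan says.** The Abstract describes a single-centre one-arm study "with indicators of feasibility as the study primary endpoints". The Hypothesis expects that "TeleGeriatrics will have good indicators of feasibility of geriatric consultations via telemedicine", in the plural. Under Primary outcome measures the protocol then lists five items:

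- **Recruitment rate:** patients agreeing to participate, "divided by total number of patients which we will have attempted to contact", so people never reached count in the denominator.
- **Attendance:** the definition reads "The attendance rate will be calculated by the proportion of virtual medical consultations completed as scheduled". The next sentence is the decision rule: "The intervention will be considered feasible if at least 80% of the consultations could be completed".
- **Acceptance:** the purpose is given as "A self-administered questionnaire will be used to evaluate whether our telemedicine intervention is feasible, safe, satisfying and well-accepted for future use". Items 1–2 of the questionnaire form a feasibility domain.
- **Discomfort:** "Patient discomfort during consultation will be assessed by the number of consultations with internet connection issues" and/or behaviour changes perceived by the interviewer, divided by the number of consultations.
- **Travel time and cost savings:** data gathered at interview on the burden of face-to-face visits.

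Only attendance has a threshold. The Statistical analysis paragraph is descriptive and does not combine the indicators.

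Two earlier sections determine who can be counted under attendance. In Study participants, patients are invited by telephone, and those who agree are screened and then booked. In Eligibility criteria, patients are excluded if they are uncomfortable with virtual consultations, lack the technology, or have no caregiver available for the visit.

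**The concern.** The subject of the 80% sentence is the intervention, not the attendance rate, and the sentence states a sufficient condition. A study that followed it literally could report home video care as feasible because booked visits took place, even if another of its primary indicators pointed the other way.

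The mismatch matters because of where attendance sits in the patient pathway. Unwillingness, lack of a device or connection, and lack of a caregiver are main ways in which telemedicine could prove unworkable for patients with dementia. All of them act before a visit is booked. The primary objective is about delivering care in Brazil's public health system, whereas the deciding rate describes a group already selected for being able and willing to use the service.

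**Working it through.** The protocol states no sample size, power or expected rate, so there is no planned figure to reproduce. The check has two parts: following the rule through the text, and an illustration with assumed rates.

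**1. What enters the rule**

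| Primary indicator | Threshold in the protocol | Enters the 80% rule? |
|---|---|---|
| Recruitment rate | none | no |
| Attendance | at least 80% | yes |
| Acceptance | none, but said to evaluate feasibility | no |
| Discomfort | none | not directly; a connection failure that ends a visit also lowers completion |
| Travel time and cost | none | no |

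**2. Who is in the attendance denominator**

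The order is: attempted contact, agreement by telephone, eligibility screening, booking, completed visit. Attendance covers only the last step. Patients who were not reached, who declined, or who were excluded are absent from both its numerator and its denominator. Attendance therefore carries no information on uptake.

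**3. Two statements about feasibility in one section**

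The Attendance paragraph says the intervention is feasible at 80% completion. The Acceptance paragraph says the questionnaire evaluates whether the intervention is feasible. The protocol does not say how the two relate, or what follows if attendance is high and the feasibility items score low.

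**4. Illustration (all recruitment rates assumed)**

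Assume one booked consultation per agreeing patient and no exclusions after agreement. Then

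share of attempted contacts with a completed visit = recruitment rate × attendance rate.

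- Worked case: 300 attempted contacts, 90 agree, 72 visits completed. Recruitment = 90/300 = 30%. Attendance = 72/90 = 80%, so the rule is met. Share = 72/300 = 24%, which equals 0.30 × 0.80.
- Attendance held at exactly 80%:

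| Assumed recruitment | Share of attempted contacts with a completed visit | 80% rule |
|---|---|---|
| 20% | 0.20 × 0.80 = 16% | met |
| 40% | 0.40 × 0.80 = 32% | met |
| 60% | 0.60 × 0.80 = 48% | met |
| 90% | 0.90 × 0.80 = 72% | met |

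The share varies more than fourfold (72/16 = 4.5) while the rule returns the same answer.

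**The case against.** The strongest reply is that the sentence stands under the Attendance heading, directly after the definition of that rate, and may have been meant only as that indicator's benchmark. The protocol repeatedly gives its aim as describing indicators, and all five will be reported whatever attendance shows. A single quantitative criterion beside descriptive results is a legitimate choice for an uncontrolled feasibility study. Further criteria could also stand in a statistical analysis plan that is not shown.

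Much of this stands. A reader might infer that the other four indicators have no bearing on feasibility, or that the plan obliges the investigators to declare success however poor they are. The documents do not support that:

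- The questionnaire is given an explicit role in judging feasibility.
- Connection failures serious enough to stop a visit lower attendance as well as raise discomfort.
- The travel data describe the burden of face-to-face care, so it is unclear what a poor value would say against telemedicine.

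A reader might also take low recruitment as proof that few patients want the service. That does not follow. The denominator is attempted contacts, which includes people never reached, and patients may be lost for want of technology or a caregiver rather than by preference.

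What remains is the wording. The sentence speaks of the intervention, and nothing in the protocol limits it to attendance. If the narrow reading was intended, the rewording below simply says so. The point does not rest on missing thresholds for the other indicators. It concerns the reach of a rule that the protocol does state.

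**Conclusion.** The concern holds in a limited form. The 80% sentence makes one of five primary indicators sufficient for an intervention-level conclusion, attendance cannot reflect low uptake, and the sentence is not reconciled with the questionnaire's stated role. The threshold of 80% is not in dispute; only its reach is.

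The size of the effect in this trial cannot be estimated, because the protocol gives no recruitment or attendance expectations. The range of 16% to 72% multiplies 80% attendance by assumed recruitment rates of 20% and 90%, and is not a forecast. The data to be collected stay usable. What is at risk is the headline conclusion.

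**What to change.** Keep the pre-specified threshold and narrow what it supports.

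1. Replace the sentence by: *The attendance criterion will be considered met if at least 80% of scheduled consultations are completed.* Limit the conclusion drawn from it to completion of visits among enrolled patients.
2. State that meeting this criterion is necessary but not sufficient for concluding that telemedicine is feasible in the public health system.
3. State that any such conclusion will be presented together with the recruitment rate, acceptance and discomfort results. For recruitment, keep attempted contacts as the denominator and count non-contact, refusal and exclusion separately. Travel time and cost remain descriptive.

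The attendance criterion should not be dropped in favour of an open judgement across all five indicators. That would remove the only criterion fixed in advance and leave feasibility to be judged after the data are seen.

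The cost is a few sentences and a tally of reasons for non-participation at the telephone and screening steps. The protocol loses its one-number overall verdict, which is a small downside.
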